### Investigators

The research team consisted of nursing specialists, community nurses, rehabilitation therapists, and postgraduate nursing students. Before implementing the intervention, all staff received comprehensive training from the principal investigator and participated in simulation training to grasp the important elements of the intervention and effectively implement it.

### Dropout and Withdrawal

Participants can withdraw at any time for any reason. They can also choose to remove their data from the study. Participants will be regarded as having withdrawn if they request to leave the trial or are lost to follow-up. Participants in the intervention group will be regarded as having withdrawn if they no longer participate in the behavior change intervention that differed from those in the control group. As this research assumes that each stage of the staircase intervention generates health effects, participants will be allowed to skip a stage but will be expected to complete the first stage and be considered to have withdrawn if they do not.

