### Study Interventions

Using the MTM as a framework and based on the review of relevant guidelines and literature, the sedentary lifestyle intervention program for community-dwelling older adults was developed (Table 1). Multimedia Appendix 1 shows the mapping of the sedentary lifestyle change interventions in the MTM, and Multimedia Appendix 2 shows the mapping of the sedentary lifestyle change interventions in the “staircase approach.” Participants in the intervention group will receive a sedentary lifestyle modification intervention based on the MTM and the staircase approach. Participants in the usual care group will receive a group education session (non-stepwise) on changing sedentary lifestyles and will be given a healthy behavior manual, an activity diary, and a pedometer.

**Table 1. T1:** The multi-theory model (MTM)–based sedentary lifestyle intervention program for community-dwelling older adults.

Timing and interventions	MTM constructs	BCTs^a^	Content of interventions	Duration/frequency
Week 1‐2, Phase I				
Discussion of advantages and disadvantages	Participatory dialogue/emotional transformation	Pros and cons	In small groups of 2‐3 people, participants engage in face-to-face communication with health educators to discuss the advantages and disadvantages of sedentary lifestyles and to identify the main factors contributing to sedentary lifestyles, concerns regarding behavior change and the home environment in order to provide personalized advice.	20 min/group
Thematic session on sedentary behavior change	Behavioral confidence	Information about health consequences Credible sources Instruction on how to perform the behavior Problem solving	This session will focus on the recognition and prevalence of SB^b^, the harms of being sedentary, the benefits of reducing sitting time, etc Peer sharing: sharing the adverse effects of long-term SB through the experiences of others, video cases, etc Recommendations for reducing SB—interrupting or replacing SB with standing or LPA^c^, household domain physical activity in different settings where it occurs, etc Give personalized guidance on the main causes of SB for each older adult. Co-discuss the barriers that participants may encounter during the process of SB change and provide practical solutions (after discussion of advantages and disadvantages).	60 min

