c LPA: light-intensity physical activity.

d PA: physical activity.

e TV: television.

f ST: sedentary time.

g MVPA: moderate-to-vigorous-intensity physical activity.

h PI: physical inactivity.

i WHO: World Health Organization.

The program for the intervention group will follow the staircase approach in the rhythm of the reduction of ST and interruption of SB through standing and moving, followed by gradual replacement of SB with LPA, and ultimately leading to increased PA and modification of a sedentary lifestyle. During weeks 1‐2, “Phase I: Sitting Less” will be implemented. This phase includes a discussion of advantages and disadvantages, thematic session on SB change, Healthy Behavior Manual, and SB interruption interventions. This component involves recognition of SB and reduction and interruption of SB through standing and activities. “Phase II: Moving More” will be implemented during weeks 3‐4. The interventions will include warning stickers, pedometer-based interventions, and activities diary. This component involves the gradual replacement of SB with LPA. “Phase III: Increasing Physical Activity and Modifying Sedentary Lifestyle” will be implemented during weeks 5‐6. The interventions will include thematic sessions on PA, introduction to health and fitness resources, and social support. This intervention aims to increase and maintain the amount of MVPA among participants. They will be encouraged to engage in all stages of the intervention, and data will also be incorporated if the participants stay at any stage of the staircase lifestyle change intervention, provided that they have attended phase I (weeks 1‐2); otherwise, they are deemed to have withdrawn.

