### Statistical Analyses

Data analyses follow intention-to-treat principles, using generalized estimating equation models to assess differential changes in the outcome variables between the 2 groups from baseline to 12 weeks (group×time interaction), with adjustment for potential covariates as appropriate (ie, baseline group differences at 2-sided *P*<.25). Effect sizes for continuous outcome variables were estimated using Cohen *d* statistic based on between-group mean differences from baseline T1 to T2, T3, and T4 end points with cutoffs set at 0.2 (small), 0.5 (medium), and 0.8 (large) [62]. Each generalized estimating equation model includes the main effects of group (intervention vs control), time (T2, T3, T4 vs baseline), and 2-way interaction effects (group×time). The group difference in the change from baseline to 6, 12, or 18 weeks between the 2 groups is verified when the 2-way interaction effects (group×time) was statistically significant. All statistical analyses are 2-sided and performed using IBM SPSS 25.0 software. *P* values <.05 is considered statistically significant.

Continuous variables that conform to normal distribution will be expressed as mean (SD) using an independent samples *t* test. Continuous variables that are not normally distributed and ranked variables will use the Mann-Whitney *U* test, expressed as median (M) and quartiles (P₂₅-P₇₅). Categorical table variables will be statistically described by frequency and percentage (%) using *χ*² test or Fisher exact test.

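### Intention-to-treat is claimed, but intervention-arm data are used only if phase I was attended, with no matching attendance rule for controls

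*Protocol article*

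**What the plan says.** Four statements in the protocol article bear on who enters the analysis.

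- **Statistical Analyses:** "Data analyses follow intention-to-treat principles, using generalized estimating equation models".
- **Study Interventions,** last paragraph: "data will also be incorporated if the participants stay at any stage of the staircase lifestyle change intervention, provided that they have attended phase I", and then "otherwise, they are deemed to have withdrawn".
- **Dropout and Withdrawal,** both arms: "Participants will be regarded as having withdrawn if they request to leave the trial or are lost to follow-up".
- **Dropout and Withdrawal,** intervention arm: "Participants in the intervention group will be regarded as having withdrawn if they no longer participate in the behavior change intervention that differed" from what controls receive. Stages may be skipped, but participants "will be expected to complete the first stage and be considered to have withdrawn if they do not".

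The control condition is described in Study Interventions: "Participants in the usual care group will receive a group education session (non-stepwise) on changing sedentary lifestyles", plus a manual, a diary and a pedometer. No attendance condition is attached to that session. The Dropout and Withdrawal section also lets any participant ask for their data to be removed, as a choice separate from withdrawing.

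**The concern.** Intention-to-treat means that everyone randomised is analysed in the assigned arm, whatever they went on to attend. Phase I attendance is observed after randomisation, and the phases exist only in the intervention arm. A rule that uses data only from phase I attenders therefore selects one arm on behaviour and leaves the other unselected. People who do not come to the first two weeks of a programme about sitting less may well be those who would have gone on sitting most. If they leave the intervention arm while their counterparts stay among the controls, the difference in sedentary time partly reflects selection.

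A second problem concerns people who attend phase I and then stop. One section appears to keep their data and the other classes them as withdrawn, so two analysts following the text could build different analysis sets.

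**Working it through.** **The plan's own figure.** The standardised effect is 120 / 142.98 = 0.839. A two-sided 5% unpaired t test has power 0.795 with 23 per group and 0.812 with 24, so the stated 24 per group reproduces. For 15% dropout, 48 × 1.15 = 55.2 (rounded up, 56) and 48 / 0.85 = 56.5 (rounded up, 57). The 60 enrolled exceed both. The sample size is not in dispute; it only supplies inputs.

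**The rules side by side.**

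| Event after randomisation | Intervention arm | Control arm |
|---|---|---|
| Asks to leave, or lost to follow-up | Withdrawn | Withdrawn |
| Does not attend the opening component | Withdrawn; data use is conditional on phase I | No rule stated |
| Attends phase I, skips a later stage | Kept | Not applicable |
| Attends phase I, then stops altogether | Data appear kept (Study Interventions); withdrawn (Dropout and Withdrawal) | No rule stated |

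The second row contradicts the intention-to-treat statement. The fourth is unresolved. The two sections also word the phase I threshold differently: one speaks of attending it, the other of completing it.

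**Illustration of size.** Inputs from the document: SD 142.98 min/d and a planned difference of 120 min/d (Sample Size Calculation); 60 enrolled at 1:1, taken as 30 per arm. Assumed, because the document gives no figure: the excluded share q of the intervention arm, and the gap g by which the excluded do worse than those retained. The comparison is a simple two-group contrast at one time point, as in the sample size calculation, not the full generalised estimating equation (GEE) model.

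The mean of everyone randomised to the intervention is the retained mean plus q × g, so dropping the share q produces a spurious benefit of q × g.

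SE = 142.98 × √(1/(30(1−q)) + 1/30)

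With no true effect, the two-sided rejection rate is Φ(−1.96 + qg/SE) + Φ(−1.96 − qg/SE).

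| q | g (min/d) | Bias (min/d) | SE | Type I error |
|---|---|---|---|---|
| 0.15 | 60 | 9.0 | 38.5 | 5.6% |
| 0.15 | 143 | 21.5 | 38.5 | 8.6% |
| 0.20 | 143 | 28.6 | 39.2 | 11.3% |

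A t-based check with whole numbers excluded and gaps of 0.25 to 1.0 SD gives:

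| Excluded out of 30 | Bias (min/d) | Type I error |
|---|---|---|
| 3 | 3.6 to 14.3 | 5.1 to 6.6% |
| 5 | 6.0 to 23.8 | 5.3 to 9.3% |
| 8 | 9.5 to 38.1 | 5.6 to 15.4% |

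**If the intervention works.** Suppose the effect is 120 min/d in attenders and zero in the 15% excluded. The intention-to-treat effect is 120 × 0.85 = 102 min/d. The restricted analysis still shows 120, an overstatement of 120/102 − 1 = 17.6%.

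**The case against.** The strongest reply is that being classed as withdrawn need not mean that data are discarded. The Dropout and Withdrawal section makes removal of data a separate choice of the participant, which suggests that withdrawal alone leaves collected data in. A repeated-measures GEE analysis can also use observations made before withdrawal.

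For people who stop after phase I, this reply largely stands. A reader might infer that they are dropped from the analysis. The text does not say so: "data will also be incorporated if the participants stay at any stage of the staircase lifestyle change intervention" points towards keeping them. That part is an ambiguity to be reconciled. Nor does permission to skip a stage contradict the rule on stopping, because missing one stage and leaving the programme altogether are different states.

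For phase I the reply fails. There the Study Interventions section makes withdrawal the alternative to having data incorporated, and nothing says that such people are still assessed or analysed as randomised. GEE does not rescue the claim. Without weighting, it generally needs missingness to be unrelated to outcome, and missingness created by non-attendance in one arm is unlikely to meet that.

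Two objections to the size also stand. The 15% in the sample size section is dropout for the whole trial from any cause, not phase I non-attendance. Sessions were repeated 2 to 4 times a week to help attendance (Adherence), so few may be affected. The upper gap of 143 min/d is a full SD, and at the lower end the type I error stays close to nominal.

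**Conclusion.** The phase I condition is wrong as written. It excludes on attendance after randomisation, in one arm only, and cannot stand beside the intention-to-treat statement. This is a conflict between two rules that the article itself states, not a detail left to an analysis plan. The handling of people who stop after phase I is unclear and needs one answer.

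The size is unknown. Bias of 9 to 21 min/d and type I error of 5.6 to 8.6% follow only if 15% of the intervention arm are excluded and would have done 60 to 143 min/d worse; with three people excluded the error is 5.1 to 6.6%. The direction, towards the intervention, rests on non-attenders doing worse, which is plausible but not documented.

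A reader might conclude that the randomised comparison is broken. The documents do not support that: they give no number of non-attenders and do not show that anyone was in fact excluded. They show a rule that, if followed, yields a selected comparison under an intention-to-treat label.

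**What to change.** Data collection was complete by May 2025, so the change lies in analysis and reporting; how participants were managed is not touched.

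1. Separate stopping the intervention from withdrawing from the study. For the analysis, define withdrawal identically in both arms: consent withdrawn or lost to follow-up.
2. Remove the phase I condition from the definition of the analysis population, and reconcile the two sections so that the status of people who stop after phase I is explicit.
3. Analyse every randomised participant in the assigned arm with all T1 to T4 data obtained, except data that a participant has asked to have removed.
4. Report the phase I attenders only as a labelled per-protocol sensitivity analysis.
5. Do not assume that outcomes exist for people deemed withdrawn; no section says they were collected. If they were not, report the numbers by arm and treat them as missing data, with a sensitivity analysis.

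The cost is revised wording, a little more analysis work and possibly a smaller estimated effect.

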### Statistical Analyses

Data analyses follow intention-to-treat principles, using generalized estimating equation models to assess differential changes in the outcome variables between the 2 groups from baseline to 12 weeks (group×time interaction), with adjustment for potential covariates as appropriate (ie, baseline group differences at 2-sided *P*<.25). Effect sizes for continuous outcome variables were estimated using Cohen *d* statistic based on between-group mean differences from baseline T1 to T2, T3, and T4 end points with cutoffs set at 0.2 (small), 0.5 (medium), and 0.8 (large) [62]. Each generalized estimating equation model includes the main effects of group (intervention vs control), time (T2, T3, T4 vs baseline), and 2-way interaction effects (group×time). The group difference in the change from baseline to 6, 12, or 18 weeks between the 2 groups is verified when the 2-way interaction effects (group×time) was statistically significant. All statistical analyses are 2-sided and performed using IBM SPSS 25.0 software. *P* values <.05 is considered statistically significant.

Continuous variables that conform to normal distribution will be expressed as mean (SD) using an independent samples *t* test. Continuous variables that are not normally distributed and ranked variables will use the Mann-Whitney *U* test, expressed as median (M) and quartiles (P₂₅-P₇₅). Categorical table variables will be statistically described by frequency and percentage (%) using *χ*² test or Fisher exact test.

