### Sample Size Calculation

The sample size was calculated using G*Power software (version 3.1.9.6) [60]. The sample size estimation refers to the standardized deviation of the self-reported ST among community-dwelling older adults obtained from a similar previous study [42]. A total of 48 older adults (24 per group) will be required to detect the effect size of 0.84, with a power of 80% (1−*β*=0.80) and a level of significance of 5% (*α*=.05, 2-tailed) by unpaired *t*-test. Using an SD of 142.98 minutes per day and an expected reduction of 120 minutes per day self-reported sitting time, a sample size of 24 patients per arm is needed. Taking a dropout of 15% into consideration, we will have at least 56 participants in our study.

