### Randomization and Blinding

Participants will be randomized in a 1:1 ratio into a behavioral intervention group, which receives a staircase MTM-based SB change intervention and a usual care group, which receives recommendations for reducing SBs. Randomization will be stratified by center, and each center will be grouped by age 65 to 75 and ≥75 years (as older adults aged ≥75 y are more likely to experience mobility impairment due to chronic conditions, resulting in higher ST compared to those aged 65‐75 y) [19,61]. Using a permuted block randomization, with a block size of 4, allocation sequences will be generated online using a website (www.randomizer.org) by an independent professional who will not be involved in subject recruitment, intervention implementation, or outcome assessment for this study, and investigators will be informed of group assignment by telephone.

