## Results

The study was initiated in May 2024. As of May 2025, the project had completed participant recruitment (60 participants) and data collection. The final manuscript with findings is expected to be submitted for publication in September 2025. This protocol is published to ensure methodological transparency and to invite peer review focused on study design.

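### With 60 participants and no small-sample adjustment named, the GEE group×time test would run at about 6% to 8% under the usual robust variance, and its handling of dropout rests on the working correlation

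*Protocol article*

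**What the plan says.** The Statistical Analyses section of the protocol article commits to intention-to-treat and to GEE models, "using generalized estimating equation models to assess differential changes in the outcome variables between the 2 groups". Each model holds group, "time (T2, T3, T4 vs baseline)" and their interaction. A group difference in change at 6, 12 or 18 weeks "is verified when the 2-way interaction effects (group×time) was statistically significant", and P "values <.05 is considered statistically significant". On sidedness and software: "All statistical analyses are 2-sided and performed using IBM SPSS 25.0 software".

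On numbers, the Results section says that "the project had completed participant recruitment (60 participants) and data collection". The Randomization and Blinding section says "Participants will be randomized in a 1:1 ratio", so about 30 per arm. The Sample Size Calculation section sets its target "Taking a dropout of 15% into consideration".

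The article names no covariance estimator, working correlation, reference distribution or small-sample correction. It does not say whether the interaction is one joint test or three separate contrasts, and it gives no missing-data assumption.

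**The concern.** GEE is usually reported with the sandwich variance and a chi-square Wald test, and both are large-sample tools. With about 25 to 30 people per arm the sandwich variance is too small on average, and the chi-square reference ignores that it is estimated. A four-level time factor gives the interaction 3 df, where the effect is larger than for a single contrast. The trial's claims rest on that P value, so a liberal test means more false claims than the stated 5%.

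The second strand is dropout. Unweighted GEE is generally valid only if dropout is completely at random. The Dropout and Withdrawal section counts intervention participants as withdrawn once they stop taking part in the intervention. Dropout can therefore differ by arm and may relate to behaviour already observed.

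**Working it through.** **The plan's own figures.** Effect size: 120/142.98 = 0.839. The noncentral t-test gives power 0.813 at 24 per group and 0.796 at 23, so 24 per group reproduces. For 15% dropout, 48/0.85 = 56.5 (57) and 48×1.15 = 55.2 (56); the 60 recruited exceed both. The sample size is not affected by this point. The figure under test is the nominal 5% level.

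**Inputs.** From the article: 4 time points, n = 30 per arm, two-sided 5%, 15% dropout (60×0.85 = 51 left, about 25 per arm), SD 142.98 min/day. Assumed, because not given: within-person correlation exchangeable 0.5, with AR(1) 0.7 and skewed data as checks.

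**Robust variance, complete data, no true effect.** With a saturated group×time mean, the sandwich covariance is (n−1)/n times the unbiased one. The Wald statistic is then n/(n−1) times a two-sample Hotelling T² with p = 3, where T² = [58×3/56]·F(3, 56).
- Joint test: reject if F(3, 56) > 7.815 × (29/30) × 56/(58×3) = 2.431. Probability **7.5%**; 7.4% by simulation.
- One contrast: reject if |t(58)| > 1.960 × √(29/30) = 1.927. Probability **5.9%**.
- At 25 per arm the same formulas give 8.0% (joint) and 6.1% (single).

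**Robust variance, 60 randomized, 15% random dropout** (fitted GEE, 5,000 replicates): joint 7.8% with independence and 8.1% with exchangeable working correlation; a single contrast about 6.1% to 6.4%. Skewed or AR(1) data without dropout give 7.1% to 7.6% on the joint test.

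**Model-based variance, exchangeable working structure, complete data.**

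| True correlation | Joint 3-df | Week 6 contrast | Week 18 contrast |
|---|---|---|---|
| Exchangeable 0.5 | 5.0% | 5.0% | 5.0% |
| AR(1) 0.7 | about 6.3% | about 2% | about 11% |

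**Corrected tests, 30 per arm, complete data.**
- Unbiased covariance with the matching F reference: joint 4.9% by simulation.
- Unbiased variance with t(58): single contrast 5.0%.
- Unbiased covariance but still chi-square: joint 6.6% by simulation. The closed form, F(3, 56) > 7.815×56/174 = 2.515, gives 6.8%.

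**Bias from dropout.** Assumed: no true effect; the intervention-arm log-odds of leaving before each follow-up are −3.2 + 1.0 × last standardised sedentary time; the control-arm log-odds are a constant −2.9; about 15% are missing at week 18. Bias at week 18, scaled by 142.98 min/day, from 12 runs of 4,000 participants:

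| True correlation | Independence GEE | Exchangeable GEE |
|---|---|---|
| Exchangeable 0.5 | −13.0 | −1.9 |
| AR(1) 0.7 | −10.0 | +4.1 |

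A negative sign favours the intervention. Simulation error is about 1.3 min/day in the first row: √(1.0×2/2,000)/√12 × 142.98. The exchangeable −1.9 is therefore hardly distinguishable from zero. The largest bias, 13.0/120, is about 11% of the planned difference.

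**The case against.** The strongest reply is that the article never says it will use an uncorrected sandwich variance or a joint 3-df test. A reader might infer that the trial's decision rule simply runs at 8% instead of 5%. The text does not support that. It describes time as each follow-up against baseline, speaks of change to 6, 12 or 18 weeks, and in one place singles out 12 weeks, all of which fit per-visit contrasts. On that reading the robust level is about 6%, a small departure. A model-based variance with the right correlation gives 5.0%. This stands: 8% is the upper end of the robust results and conditional on two choices.

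The model-based route is no safe escape, however. Correlation that decays over 18 weeks is plausible, and an exchangeable model-based variance can then be badly off at single visits, in both directions.

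A reader might also infer that every P value and confidence interval is too optimistic, or that GEE is invalid unless dropout is completely at random. Neither follows. The week 6 contrast can even be conservative under a model-based variance. Completely random dropout is the general condition, but with a near-correct working correlation the bias is small. That departure depends on earlier sitting time is an assumption; the article ties intervention-arm withdrawal to participation.

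Finally, estimator settings may properly sit in an analysis plan that is not shown, so their absence is not the point here. What the article does fix is GEE, the number of participants and the significance rule. For that combination a better calibrated method exists in the same software.

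**Conclusion.** The concern holds in conditional form. With 60 participants and the usual robust variance and chi-square reference, the joint interaction test runs at about 7.5% with complete data and about 8% with 15% dropout; a single-visit contrast runs at about 6%. A model-based variance keeps 5% only if the working correlation is right. The dropout strand is real but modest: about 2 to 4 min/day with an exchangeable structure and 10 to 13 with independence, under one assumed mechanism, against 120 planned.

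The levels rest on assumed correlations and mainly normal data, but the robust-variance results moved little across the structures tried. This is a cheap improvement, not an error that invalidates the trial. Calling a difference shown if any of three contrasts is significant would give about 14% to 16%; that is mostly multiplicity, a separate matter not counted here.

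**What to change.** For approximately normal continuous outcomes, replace GEE by a linear mixed model for repeated measures: group, time and group×time, unstructured covariance over the four visits, REML, Satterthwaite degrees of freedom. SPSS offers this in its MIXED procedure. If correctly specified, it is valid when dropout is at random given the observed data. Alternatively, keep GEE with a bias-corrected covariance and a t or F reference; correcting the covariance alone still leaves about 6.6% on the joint test. For bout counts and skewed activity minutes, keep corrected GEE or add a bootstrap check. In either case state whether the interaction is tested jointly or per visit.

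The mixed model is not perfect for a joint test. With 30 per arm and complete data, an unscaled F on 3 and 58 df rejects when F(3, 56) > 2.764×56/58 = 2.668, a level of about 5.6%. Its single-visit contrasts are at 5.0%.

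The cost is a different procedure in the same software, no new data, and a residual normality assumption that diagnostics can check. Because data collection is complete, the change must be documented with its date before unblinded analysis. If that is no longer possible, report it as a sensitivity analysis beside the published GEE.

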### Study Measurements

#### End Points

The duration of the intervention is 6 weeks with 12 weeks of follow-up. Outcome measures were collected at baseline T1, end of intervention (week 6) T2, week 12 (T3), and week 18 (T4; Figure 2). The primary endpoint is the change in self-reported ST (total ST and SB characteristics, such as screen-based ST, longest continuous ST, and number of sedentary bouts ≤30 min). Secondary endpoints include the changes in step count (steps/d), time spent in LPA (min/wk), time spent in MVPA (min/wk), the Short Physical Performance Battery (SPPB) score, blood pressure, Measuring Change in Physical Activity Questionnaire (MCPAQ) score, waist circumference, BMI, and quality of life (SF-12v2 score) (Table 2).

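### The planned group×time GEE is a change-score analysis, less precise than adjusting for the baseline value; if 142.98 is the SD of sedentary time itself, the stated power depends on an unstated correlation

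*Protocol article*

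**What the plan says.** End Points defines the primary outcome as a change: "The primary endpoint is the change in self-reported ST", measured at baseline and at weeks 6, 12 and 18 (T1 to T4).

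Statistical Analyses specifies the model: "Each generalized estimating equation model includes the main effects of group (intervention vs control), time (T2, T3, T4 vs baseline), and 2-way interaction effects". The treatment effect is read from the group×time interaction. Covariates enter only if the arms differ on them at baseline at P<.25. The section names no working correlation and no routine adjustment for the baseline value of the outcome.

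Sample Size Calculation sizes the trial "by unpaired *t*-test", at 24 per group, "to detect the effect size of 0.84, with a power of 80"%. Its inputs are given as "Using an SD of 142.98 minutes per day and an expected reduction of 120 minutes per day self-reported sitting time". On the source of the SD it says: "The sample size estimation refers to the standardized deviation of the self-reported ST among community-dwelling older adults". It states neither an SD of change nor a baseline–follow-up correlation. The target after 15% dropout is at least 56, and Results reports 60 enrolled.

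**The concern.** There are two linked issues.

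The first is precision. Randomisation makes the true baseline means of the two arms equal, yet the model estimates them separately and subtracts them. Baseline is therefore used with its coefficient fixed at 1, whatever its actual relation to follow-up. Letting the data set that coefficient never gives a larger large-sample variance and usually gives a smaller one. In a trial of 60 the difference can matter.

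The second is that sizing and analysis may not match. The sizing appears to use the SD of sedentary time at one occasion, while the quantity tested is a change. These SDs coincide only at one value of a correlation that the protocol does not give, so the stated 80% would carry a hidden assumption that a baseline-adjusted analysis does not need.

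**Working it through.** **Inputs from the protocol.** Difference 120 min/day; SD 142.98 min/day; two-sided 5%; 24 per arm; 1:1 allocation; 60 enrolled; 15% dropout. **Assumed:** rho, shown over a range; equal variance at baseline and follow-up, except in step 3; complete data.

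**1. The stated sample size reproduces.** d = 120/142.98 = 0.839. Noncentral-t power is 79.5% at 23 per arm and 81.2% at 24, so 24 per arm is correct for an unpaired t-test with that SD.

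**2. What the interaction estimates.** In simulated complete data (24 per arm, four visits), the three interaction coefficients equalled the between-arm differences in mean change exactly, under both independence and exchangeable working correlation. Adding a time-constant covariate as a main effect, even baseline sedentary time itself, left the interaction coefficients and their standard errors unchanged. The P<.25 rule therefore does not recover the lost precision.

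**3. Variance of the two analyses.** With common SD σ:
- change: σ²·2(1−rho)
- baseline-adjusted: σ²·(1−rho²)
- ratio: 2(1−rho)/[(1−rho)(1+rho)] = 2/(1+rho)

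The direction does not need equal variances. With baseline SD σ₀ and follow-up SD σ₁, the change variance minus the adjusted variance is σ₀² + σ₁² − 2·rho·σ₀σ₁ − σ₁²(1−rho²) = (σ₀ − rho·σ₁)², which is never negative.

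**4. Power for one visit at 24 per arm, if 142.98 is the SD of the level.** SD of change = 142.98·√(2(1−rho)); adjusted SD = 142.98·√(1−rho²).

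| rho | SD of change | Power, planned | Power, adjusted | Variance ratio |
|---|---|---|---|---|
| 0 | 202.2 | 52% | 81% | 2.00 |
| 0.2 | 180.9 | 61% | 83% | 1.67 |
| 0.3 | 169.2 | 67% | 85% | 1.54 |
| 0.4 | 156.6 | 74% | 87% | 1.43 |
| 0.5 | 143.0 | 81% | 91% | 1.33 |
| 0.6 | 127.9 | 89% | 95% | 1.25 |
| 0.7 | 110.8 | 96% | 98% | 1.18 |

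The SD of change equals 142.98 only at rho = 0.5. The adjusted column ignores the one degree of freedom spent on the covariate.

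**5. Where the planned analysis reaches 80%.** Rho = 0.48 at 24 per arm. With 60 enrolled and 15% loss (60 × 0.85 = 51, or 25.5 per arm), rho = 0.45. With all 30 per arm retained, rho = 0.35. At rho = 0.3 and 30 per arm, power is 77%.

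**6. Joint test of the three interactions.** With a constant effect at all visits and 24 per arm, simulated power was 71%, 75% and 88% at rho 0.2, 0.3 and 0.5 (a large-sample test, slightly liberal). The correlation needed is therefore somewhat lower than for one visit.

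**7. Check on one possible remedy.** Dropping the group main effect imposes a common baseline mean. In a GEE with independence working correlation, each group×time coefficient then becomes the raw follow-up difference. At rho = 0.7 and 24 per arm the theoretical standard errors are:
- raw difference: 142.98·√(2/24) = 41.3
- planned change: 110.8·√(2/24) = 32.0
- baseline-adjusted: 102.1·√(2/24) = 29.5

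So that remedy under independence is worse than the planned model. In simulation (400 replicates) it gave 41.0 under independence and 28.6 under exchangeable, against 30.3 for the planned model.

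**The case against.** The strongest reply is that the planned GEE is a valid analysis, unbiased under randomisation, and that it does use baseline. This stands: the issue is efficiency only, and the excess variance is modest (18%) when rho is 0.7.

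A reader might infer from the table that the trial is underpowered. The documents do not support that, for four reasons:
- Rho appears nowhere. The ST and PA section describes the questionnaire's reliability as favourable but gives no correlation, so nothing shows that rho is low.
- The SD comes from a previous study that is not at hand. The wording points to the SD of the level, but a loosely described SD of change cannot be excluded. In that case power for the change contrast is 81% whatever rho is.
- More were enrolled than the 48 required, which lowers the threshold to between 0.35 and 0.45, depending on losses.
- The percentages are for one visit. A joint test of the three interactions does somewhat better if the effect is constant.

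Entry requires more than 6 hours of sitting per day, which may narrow the baseline spread, so equal variances are an approximation. The exact ratios would shift, but step 3 shows that the direction would not.

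Finally, data collection was complete by May 2025. Changing the published model now needs a documented reason and is more than a change of syntax. That is a fair cost, but no reason to keep the less precise analysis as primary.

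**Conclusion.** The efficiency point holds on the protocol's own model. The interaction is a difference in mean change; with equal variances its variance exceeds that of a baseline-adjusted analysis by 54%, 33% and 18% at rho 0.3, 0.5 and 0.7; and the covariate rule does not close the gap. The equality with the difference in mean change is exact for complete data and approximate with missing visits.

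The power point is conditional. If 142.98 is the SD of sedentary time, the stated 80% at 24 per arm requires rho of about 0.48 or more for a single visit, an assumption the protocol does not state. The baseline-adjusted analysis needs no such assumption. If 142.98 is an SD of change, only the efficiency point remains.

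There is no bias and no demonstrated shortfall. The change is worth making because the sample size can no longer be altered, while the precision of the analysis can.

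**What to change.** In Statistical Analyses, for continuous outcomes, model T2, T3 and T4 as the outcome with group, time, group×time, the baseline value of that outcome and baseline×time. Read the group difference at each visit.

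A common-baseline model (baseline kept as an outcome row, no group main effect) is acceptable only with a stated non-independence working correlation, such as exchangeable or unstructured. Under independence it ignores baseline and can be less precise than the present plan.

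Record the change and its reason before any comparison by arm, and keep the published model as a sensitivity analysis.

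In Sample Size Calculation, state whether 142.98 is the SD of the level or of the change. Then give the power either with its assumed rho or on the baseline-adjusted model.

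Cost: a documented change to a published model after data collection, and one or a few degrees of freedom. No new data are needed.
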